### Evidence for MS rehabilitation

A recently updated version (April 2011) of a Cochrane review [6] identified ten studies of varying quality and concluded that although MS rehabilitation may have limited effect on body functions, short-term improvement in activity and participation could be observed. Another Cochrane review suggested that exercise therapy might be beneficial for muscle power function, exercise tolerance, mobility-related activities and mood in patients with MS, although no clear effects could be identified in relation to fatigue or perception of handicap [7].

The efficacy and cost-effectiveness of the Sclerosis Hospitals rehabilitation program for MS patients were investigated in a longitudinal study [8], in which participants completed a single outcome instrument (FAMS questionnaire) to measure quality of life at referral, admission, discharge and up to five months after discharge. The study showed an increase in the FAMS score from referral and admission to discharge and thereby identified a statistically significant improvement in quality of life. Although the FAMS scores had decreased five months after discharge, there was still a statistically significant improvement compared with the score at referral. The study had a number of design issues that complicated assessment of the rehabilitation effort. As the study had no control group, part of the observed effect may have been due to factors other than the rehabilitation program. The considerable variation in participants' personal and disease-related factors could also have influenced the observed effects.

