### Study objectives

The aim of the planned study is to document the effects of a highly personalized rehabilitation program for MS patients as provided by the Sclerosis hospitals using a randomized controlled study design and standard generic and disease-specific outcome measures. The objective is to assess the program’s effect on patients in terms of changes in disease-specific quality of life and to answer the following questions:

To what extent are the observed effects maintained six and twelve months after discharge?

How do different dimensions of quality of life, functional ability, mastery, coping, compliance and specific measurements of sleep, daily activities, gait, balance and activity limitations correlate?

What individual goals are set before the start of the rehabilitation?

What are the central areas and priorities of the personalized rehabilitation program?

What specific and measurable actions are included in the personalized rehabilitation program?

What effect does the rehabilitation process have on individual patient’s goals and priorities at discharge?

To what extent do patients maintain coping, one month after discharge?

What resource use and costs occur for patients and their relatives, and for the rest of the health care system?

What is the relationship between the obtained effects and costs?

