## Methods and design

The study is designed as a pragmatic clinical trial [9] of a complex intervention with personalized outcomes [10]. It attempts to maximize external validity by incorporating important features of the rehabilitation intervention in real-life settings and allowing individual participant-selected treatment goals and personalized outcomes.

The study design (Figure 1) is a two-hospital controlled trial of the rehabilitation intervention with randomization to either early admission (‘intervention group’; admission within two months after referral and clinical prescreening) or usual admission (‘control group’; admission approximately eight months after referral to the hospital and clinical prescreening). Any differences between these two groups on observed measures between baseline and six-month assessments will be considered as effects of the rehabilitation program. As the control-group patients are admitted to the hospitals after approximately eight months from referral and prescreening, they also contribute with data to the effect of personalized rehabilitation. To observe long-term effects, data collection will be repeated after twelve months.

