### Comparative analysis

The following comparative analysis will be conducted:

Difference from Time A1 to Time A5 for intervention group compared with the difference from Time B1 to Time B2 for control group (i.e. difference in outcomes for rehabilitation vs. no rehabilitation at 6-month follow-up)

Difference between Time A1 and Time B1 (i.e. difference between intervention and control group at baseline)

Difference between Time A1 and Times A5 and A6 (i.e. baseline vs. 6- and 12-month follow-up for intervention group)

Difference between Time B3 and Time B6 for control group (i.e. admission vs. 12-month follow-up).

Difference between A2 and A3 for intervention group (pre- vs. post-hospital rehabilitation)

Difference between B3 and B4 for control group (pre- vs. post-hospital rehabilitation).

Difference between Time A1 and Time A4 for intervention group A (baseline vs. one month after hospital rehabilitation)

Difference between Time B3 and Time B5 for control group (pre- vs. one month after hospital rehabilitation)

Changes in Mastery (heiQ) over time: Times A1, A4, A5 and A6 for intervention group compared with Times B1, B2, B5 and B6 for control group

Subgroup analyses will be performed on the individual focus areas, based on data from participants who have completed the goal-related questionnaires.

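### The discharge contrasts, the pairwise one-month contrasts and the controls' later contrast are uncontrolled before-after changes, yet the protocol treats such data as showing an effect of rehabilitation

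*Protocol article*

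**What the plan says.** Under Evidence for MS rehabilitation, the protocol article gives a main limitation of the earlier before-after study of this programme: "As the study had no control group, part of the observed effect may have been due to factors other than the rehabilitation program".

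Study objectives then asks: "What effect does the rehabilitation process have on individual patient’s goals and priorities at discharge". Methods and design attributes between-group differences from baseline to six months to the programme. It adds that the controls are admitted after about eight months, and that "they also contribute with data to the effect of personalized rehabilitation".

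For discharge, Comparative analysis lists "Difference between A2 and A3 for intervention group (pre- vs. post-hospital rehabilitation", and for the controls the matching change from B3 to B4. For one month it lists "Difference between Time A1 and Time A4 for intervention group A (baseline vs. one month after hospital rehabilitation", and for the controls the change from B3 to B5.

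It also lists B3 to B6 within the control group. Two listed longitudinal comparisons are between groups. One is the six-month contrast, A1 to A5 against B1 to B2. The other is heiQ over time, at "Times A1, A4, A5 and A6 for intervention group compared with Times B1, B2, B5 and B6 for control group".

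**The concern.** A change within one group contains the programme's effect together with everything else that moves the score: natural course, regression to the mean, and the act of being re-scored. The setting makes such movement likely. Patients enter when they are referred for help. MYCaW scores two self-selected problems for which the patient seeks help, and the goals come from the area the patient names as most important. These measures are scored at the preparation day and again at discharge.

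The trial has the untreated group that the earlier study lacked, but the listed discharge contrasts and the pairwise one-month contrasts do not use it. By the time controls reach B3 to B6, no untreated patients remain. If these changes are read as effects, the conclusions at discharge, and for the controls after admission, are no better protected than those of the study the protocol criticises.

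**Working it through.** **1. Which contrasts have an untreated reference**

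| Listed contrast | Type | Untreated reference |
|---|---|---|
| A1–A5 vs B1–B2 | between groups, randomised | yes, same interval |
| heiQ: A1, A4, A5, A6 vs B1, B2, B5, B6 | between groups | B1 and B2, but none at the time of A4; B5 is after treatment |
| A2–A3, B3–B4 | within group | none |
| A1–A4, B3–B5 | within group | none |
| B3–B6 | within group | none; all patients are due to have been admitted |

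**2. Which instruments could have a reference (Table 2)**

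- Discharge: FAMS, MSIS-29 and EQ-VAS are collected at B1, B2 and discharge.
- One month after discharge: FAMS and heiQ are collected at B1, B2 and one month.
- MYCaW, the goal-related outcomes and motor and process skills (AMPS) have no B2 entry. Table 2 therefore provides no untreated change for them.
- The outcome section schedules physical tests at inclusion and at six months. That would give controls untreated values, but it does not match the goal-related rows of Table 2.

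**3. The protocol's own figures reproduce**

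The inputs are from Sample size calculation: FAMS SD 27 (alternative 20), a 5-point difference, alpha 5% (two-sided reproduces the figures) and correlation 0.8.

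n per group = 2 × (SD/5)² × (z for alpha + z for power)²

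- SD 27, 90% power: 2 × (27/5)² × (1.960 + 1.282)² gives 613. At 80% power it gives 458. Both match.
- 10 points: 154 and 115. SD 20 at 80% power: 252. All match.
- The 160 and 120 come from multiplying the SD 27 variance by (1 + 0.8)/2 − 0.8² = 0.26.

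**4. How often a before-after test is significant with no treatment effect**

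Take n = 200 with complete data and r = 0.8.

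- SD of change = SD × √(2(1 − r)). This is 27 × √0.4 = 17.08, or 20 × √0.4 = 12.65.
- SE = SD of change / √200 = 1.207, or 0.894.
- For a drift d unrelated to treatment, P(significant) = Φ(d/SE − 1.96) + Φ(−d/SE − 1.96).

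| Assumed drift (FAMS points) | SD 27 | SD 20 |
|---|---|---|
| 0 | 5% | 5% |
| 1 | 13% | 20% |
| 2 | 38% | 61% |
| 3 | 70% | 92% |

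Worked line for 2 points at SD 27: 2/1.207 = 1.657, and Φ(1.657 − 1.96) = Φ(−0.303) = 0.381. All three non-zero drifts are below the 5 points that the protocol calls clinically significant. The documents give no drift, so its size is an assumption.

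**5. Whether a referenced contrast is affordable**

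With the full untreated change as reference, the SE of the difference is 17.08 × √(2/200) = 1.708 at SD 27, or 12.65 × √(2/200) = 1.265 at SD 20. Power for 5 points is Φ(5/1.708 − 1.96) = 83%, or Φ(5/1.265 − 1.96) = 98%.

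**6. Timing**

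Admission within two months plus a four-week stay puts A3 at up to about month three and A4 at up to about month four. The untreated values are at months 0 and 6. Linear interpolation credits about 3/6 of the untreated change by A3 and 4/6 by A4. Using the full B1–B2 change credits all of it, which suits a change that comes soon after referral.

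**The case against.** The strongest reply is that the protocol ties its main attribution to the randomised six-month contrast and lists it first. Comparative analysis labels the other contrasts neutrally, as before against after, and does not call them effects. The one-month objective asks whether coping is maintained, for which follow-up within a group is natural. Only FAMS and heiQ are taken one month after discharge, and heiQ has a between-group comparison. Random effects models are planned and could use the untreated data; their exact contrasts may sit in an analysis plan not shown here.

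Much of this stands. A reader might infer that the whole trial repeats the earlier study's flaw, or that everything at one month is uncontrolled. The documents support neither. What remains is that Study objectives asks about an effect at discharge, Methods and design counts the controls' later data towards the effect, and the article itself lists within-group contrasts for both. That is stated text, not detail left to another document.

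Two further inferences go too far:

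- **A large gain because patients choose their worst area.** The preparation-day section says they name the most important area. The areas use different instruments, so such a gain cannot be set against the FAMS threshold.
- **B3 less comparable with A2 because the relapse rule applies only at the neurological appraisal.** A2 can also fall up to about two months after the appraisal. No listed contrast compares the two periods, and no relapse rate is given.

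**Conclusion.** The point holds in limited form. A2–A3, B3–B4, A1–A4, B3–B5 and B3–B6 are uncontrolled before-after changes, and the objectives and design text treat such data as evidence of effect. The six-month result is sound. The heiQ comparison is partly controlled, without a time-matched untreated value for A4.

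On the protocol's FAMS inputs, an assumed drift of 2 points would be declared significant 38% of the time at SD 27 (61% at SD 20) with no treatment effect. This rests on 200 complete pairs, correlation 0.8 and a drift the documents do not quantify. Drift could also run the other way in a progressive disease and hide a benefit; either way the contrast cannot tell. It does not follow that the uncontrolled gains would exceed the six-month result, since nothing in the documents gives their size. The change is worth making because it decides what the trial may claim at discharge.

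**What to change.** - **Wording.** In Study objectives, Methods and design and Comparative analysis, label these contrasts as descriptive change and keep the word effect for contrasts with an untreated reference. State that changes in MYCaW, goal scores and AMPS, which have no B2 value in Table 2, do not by themselves show an effect.
- **Model contrast.** For FAMS, MSIS-29 and EQ-VAS at discharge (A3), and FAMS and heiQ at one month (A4), estimate the effect in the planned random effects model against the controls' untreated B1–B2 course.
- **Sensitivity.** Report each estimate twice: with linear interpolation between months 0 and 6, and with the full B1–B2 change as reference.

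Subtracting the controls' B1–B2 change from their own B2–B4 change is not a good substitute. Regression soon after referral falls mainly in the first interval, so the subtraction would over-correct.

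The cost is wording and a few model contrasts on data already planned. The drawbacks are that the untreated course between months 0 and 6 must be assumed, and that goal-related results at discharge can be reported only as change.

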**Figure 1 F1:**
[figure not shown]
Patient selection for a randomized study of a MS rehabilitation program.

### Participants

Study participants will be recruited among all patients referred to the four-week individual rehabilitation program during March 2012 to June 2013. Patients referred for shorter rehabilitation programs or theme courses will not be eligible for the study.

Participants must meet the following inclusion criteria: aged between 18 and 65 years; diagnosis of MS (relapsing remitting, primary or secondary progressive MS); Expanded Disability Status Scale (EDSS) score ≤ 7.5 [11]; can use a personal computer or has a support person/relative who can; ability to read and understand sufficient Danish to understand instructions both orally and in writing; completion of written informed consent.

The following exclusion criteria will apply: less than six months between diagnosis of MS and referral to the program; disease relapse within three months of the neurological appraisal; recipient of sclerosis-specific hospital-based rehabilitation within the last six months; cognition score (KFS) > 2 or cognitive limitations which hinder completion of self-reported questionnaires and/or informed consent; severe depression; severe heart or lung disease; drug or alcohol abuse; any other illness that can impede participation in the study. If participants develop a disease that might impair their participation in the study they will be excluded from the study at that time.

The final decision on participant inclusion or exclusion will be based on the physician/neurologist assessment.

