### Descriptive analysis

Differences in personal and disease characteristics will be compared between participants completing the study, those who fulfill the inclusion criteria but decline participation (primary drop-out), and those who participate in parts of the study but for various reasons end participation (secondary drop-out). We will investigate for specific characteristics that distinguish drop-out individuals from those who complete the study.

The included study population will be described and the intervention and control groups will be compared for eventual significant differences in personal and disease characteristics. 'Intention to treat' analysis will be used for comparing the efficacy of the two groups and longitudinal random effects regression models (panel analysis) will be applied.

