### Blinding

It is not possible to blind participants in relation to which group they are randomized to. Similarly, it is not possible to blind the staff at the two hospitals regarding participation in the study and randomization group. Study participants will be admitted to the rehabilitation program concurrently with non-participants. This means that the intervention group and control group will be treated alongside patients outside the study.

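### The rule excluding participants who fall ill during the study is not reconciled with the intention-to-treat comparison and can bias the six-month contrast

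*Protocol article*

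**What the plan says.** The Participants section lists the eligibility criteria, including an exclusion for other illness present at entry, and then adds: "If participants develop a disease that might impair their participation in the study they will be excluded from the study at that time". The section closes with: "The final decision on participant inclusion or exclusion will be based on the physician/neurologist assessment".

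Under Descriptive analysis, an intention-to-treat "analysis will be used for comparing the efficacy of the two groups and longitudinal random effects regression models (panel analysis) will be applied". The same section mentions "those who participate in parts of the study but for various reasons end participation (secondary drop-out", but only as a group whose characteristics will be set against those of completers.

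The main contrast, under Comparative analysis, is: "Difference from Time A1 to Time A5 for intervention group compared with the difference from Time B1 to Time B2 for control group". The Methods and design section interprets it this way: "Any differences between these two groups on observed measures between baseline and six-month assessments will be considered as effects of the rehabilitation program". Under Blinding, the article states that "it is not possible to blind the staff at the two hospitals regarding participation in the study and randomization group".

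No section says whether a participant excluded for a new disease is still followed up or kept in the comparison.

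**The concern.** Intention to treat needs the six- and twelve-month outcomes of everyone randomised, whatever happens to them in between. The exclusion sentence works against this. It takes people out because their health has changed, and health is what the outcomes measure. Those removed are likely to be patients whose quality of life has fallen.

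Three features make unequal removal plausible:

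- **Open criterion.** A disease that might impair participation is a judgement with no objective threshold.
- **Knowledge of allocation.** The judgement is a physician's or neurologist's, in a trial whose hospital staff know the arm.
- **Different exposure before six months.** The early arm has a preparation day, a four-week admission, discharge tests and a one-month follow-up. The control arm has no admission until about eight months. A new illness is more likely to be noticed in the early arm, and the same illness has more participation to impair there.

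At stake is the main result. The article attributes any six-month difference to the programme, which leaves no room for a difference produced by who was removed.

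**Working it through.** **1. Does the rule act after randomisation?** Illness present at entry already has its own exclusion criterion. The extra sentence concerns disease that develops later, with removal when it occurs. Follow-up runs to twelve months after baseline, so nearly all the time it can cover is after randomisation. It sets no limit to the period before.

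**2. What is lost?** On the mildest reading, earlier data are kept in the allocated arm and only later collection stops. A random-effects model then uses what was observed and is valid if missingness depends only on observed data. By Table 2, FAMS in the control arm is measured at B1 and next at B2. A control excluded between them has only a baseline value, which cannot reflect the new illness. An early-arm patient may also have FAMS at discharge (A3) and one month later (A4). The model therefore has less to work with in controls.

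**3. The article's own figures.** It gives none for exclusions. The yardstick is the 5-point FAMS target under Sample size calculation, which reproduces:

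n per arm = 2 × (1.960 + 1.282)² × 27² / 5² = 613 (90% power), as stated. The figures of 458, 154, 115 and 252 also reproduce. None is in dispute.

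**4. Size of the bias under no true effect.** Let f be the share excluded in an arm and D the amount by which the excluded would have changed worse than those retained, with D the same in both arms. If the full-arm mean change is 0 and the retained mean is R:

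(1 − f)R + f(R − D) = 0, so R = fD.

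Bias (early minus control) = (f_early − f_control) × D.

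Both inputs are assumptions:

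| Imbalance | D (FAMS points) | Bias (points) | Share of 5-point target |
|---|---|---|---|
| 0 | any | 0 | 0% |
| 0.02 | 10 | 0.2 | 4% |
| 0.05 | 20 | 1.0 | 20% |
| 0.10 | 20 | 2.0 | 40% |

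With 200 per arm, imbalances of 2 and 10 percentage points are 4 and 20 patients. Higher FAMS is better, so more exclusions in the early arm would favour the programme and more in the control arm would work against it. The formula treats excluded patients as contributing nothing. A model that uses their earlier values could reduce the bias.

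**5. Effect on the false-positive rate.** Assume 185 analysed per arm and the article's correlation of 0.8. Change-score SD = SD × √(2 × (1 − 0.8)), which is 12.65 for SD 20 and 17.08 for SD 27. Standard error = change SD × √(2/185), which is 1.32 and 1.78. Two-sided type I error at a nominal 5%:

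| Bias (points) | SD 20 | SD 27 |
|---|---|---|
| 0.5 | 6.7% | 5.9% |
| 1 | 11.8% | 8.7% |
| 2 | 33.0% | 20.3% |

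**6. Loss of numbers matters less.** On the same change scores, going from 200 to 180 per arm lowers power for 5 points from 0.977 to 0.963 (SD 20) or from 0.833 to 0.793 (SD 27).

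**The case against.** The strongest reply is that this is ordinary missing data. Being excluded from the study need not mean that data are deleted or that the patient leaves the allocated arm. The article foresees people who end participation early and names a longitudinal model that can use partial data. Details of handling belong in a fuller document. This stands in part. A reader might infer that the rule flatly contradicts intention to treat by removing patients from the analysis set, and the text does not say so. But the point concerns a rule the article states, not a detail it omits, and even on the mild reading that rule creates the missing outcomes.

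Other stronger readings also go beyond the text:

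- **That unblinded staff make these exclusions.** This joins two sections. No section says who would judge a disease arising during follow-up, or that this person knows the arm.
- **That exclusion will be unequal.** Contact before six months differs, but both arms have EDSS and a walking test at the six-month point (A5 and B2), and nothing shows that unequal removal follows.
- **That the range in the working estimates the bias.** It does not. Its upper end needs about 20 more exclusions in one arm of 200, among patients aged 65 or under already screened for serious illness. Its lower end is negligible.

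It is also fair to say that the sentence could cover the short interval between consent and randomisation. If that was the intention, the text should say so. Register data on resource use and vital status are planned, and nothing says they stop on exclusion, so part of the follow-up may already be secured.

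**Conclusion.** The concern holds in a limited form. The exclusion sentence, as worded, applies after randomisation and is not reconciled with the intention-to-treat comparison. At the least it ends outcome collection for a health-related reason, which the random-effects model corrects only if missingness depends on observed data. It can bias the A1–A5 versus B1–B2 contrast.

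Whether it does, how far and in which direction cannot be found from the article. The bias is nil if exclusion and prognosis are equal in the two arms. The range of 0.2 to 2.0 FAMS points rests wholly on the assumed imbalances and gaps. It shows that the upper part would matter against a 5-point target, not that it is expected. The case for changing the text is that outcomes never collected cannot be recovered at analysis.

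**What to change.** Reconcile the Participants and Descriptive analysis sections. State that the exclusion sentence applies only before randomisation, and add wording such as:

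> A participant who develops another disease after randomisation stays in follow-up unless consent is withdrawn: online questionnaires at six and twelve months, register data, and visit-based tests where feasible. The participant is analysed in the arm to which he or she was allocated. Reasons for and timing of any discontinuation are reported by arm.

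This concerns data collection and analysis only. Decisions on care stay with the treating physician.

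The cost is modest, because the online questionnaires and register extracts are already planned. It does require some follow-up effort, and outcomes will vary slightly more. The remedy is partial: EDSS, walking and other physical tests need attendance, some illnesses prevent self-report, and some of these values will still be missing.
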